## Abstract

**Background:**

The coronavirus-19 (COVID-19) has reached pandemic status and is affecting countries all over the world. The COVID-19 pandemic is accompanied by various stressors that require adjustment in everyday life and possibly changes in personal future prospects. While some individuals cope well with these challenges, some develop psychological distress including depressive symptoms, anxiety, or stress. Internet-based self-help interventions have proven to be effective in the treatment of various mental disorders such as depression and anxiety. Based on that, we developed an internet-based self-help program for individuals with psychological distress due to the situation surrounding the COVID-19 pandemic. The 3-week self-help program consists of 6 modules comprising texts, videos, figures, and exercises. Participants can request guidance within the self-help program (guidance on demand). The primary aim of this study is to evaluate the efficacy and feasibility of the self-help program compared to a waiting control condition.

**Methods:**

The design is a parallel group randomized controlled trial. Participants are allocated to a 3-week self-help intervention plus care as usual or a 3-week waiting period with only care as usual. There are follow-ups after 6 weeks and 18 weeks. At least 80 participants with COVID-19 pandemic related psychological distress will be recruited. Primary outcome are depressive symptoms. Secondary outcomes include anxiety and chronic stress, suicidal experiences and behavior, health-related quality of life, generalized optimism and pessimism, embitterment, optimistic self-beliefs, emotion regulation skills, loneliness, resilience, and the satisfaction with and usability of the self-help program.

**Discussion:**

To the best of our knowledge, this is one of the first studies investigating the efficacy of an internet-based self-help program for psychological distress due to the situation surrounding the COVID-19 pandemic. Thus, the results of this study may give further insight into the use of internet-based self-help programs in pandemic-related psychological distress.

**Trial registration:**

ClinicalTrials.gov NCT04380909. Retrospectively registered on 8 May 2020.

## Administrative information

The order of the items has been modified to group similar items (see http://www.equator-network.org/reporting-guidelines/spirit-2013-statement-defining-standard-protocol-items-for-clinical-trials/).

## Introduction

### Background and rationale {6a}

The coronavirus-19 (COVID-19) has reached pandemic status and is affecting countries all over the world. Health systems are facing major challenges: In addition to the risks for physical health, the COVID-19 pandemic also represents a burden for mental health [1]. Pandemic-related stressors such as quarantine, social isolation/distancing, unemployment, financial losses, caregiver stress, and confrontation with illness and death can have a negative impact on mental health [1]. For example, in a study on the severe acute respiratory syndrome (SARS) pandemic, approximately 40% of the study population experienced increased stress related to work, finances and family and 16% showed signs of posttraumatic stress [2]. Preliminary research on the psychological impact of the COVID-19 pandemic indicates increased levels of psychological distress in the general population [3, 4]. Symptoms of anxiety, depression, and self-reported stress are suggested psychological reactions to the COVID-19 pandemic [5, 6].

Although pandemics comprise a multitude of stressors that may strain mental health, not everybody is experiencing psychological distress in response. Moreover, individuals might differ in the amount and kind of stressors they are exposed to, and therefore, some individuals might be at higher risk for mental health problems [7]. Some of the stressors that occur during a pandemic can be considered critical life events (e.g., death of loved ones and job loss) and require adjustment to changed life circumstances [8]. A lack of adjustment can lead to psychological distress, for example expressed in a change of one’s psychological condition. This can include experiencing depressive and anxiety symptoms [9]. Furthermore, maladaptive adjustment to critical life events might eventually lead to full-blown mental disorders like adjustment disorders (AjD) or depression [10–12].

Some recommendations for interventions targeting psychological distress due to the COVID-19 pandemic have been made: Firstly, cognitive behavioral therapy (CBT), in particular the restructuring of thought patterns and cognitive thinking traps, as well as activity planning and relaxation techniques are considered suitable interventions [6, 13]. Secondly, digital aids such as internet-based self-help interventions are encouraged, as they do not require physical contact and are easily scalable [6, 14, 15].

The efficacy of internet-based self-help interventions for various psychological problems is established [16, 17]. However, internet-based interventions can differ in their design, especially in the degree of therapist support that they offer. While some internet-based interventions offer contact with a therapist (guided self-help) other interventions are completely automated (unguided self-help). Moreover, guided self-help interventions can differ in the intensity of provided contact. On the one hand, guided self-help programs yield higher effect-sizes and have higher retention rates than unguided self-help programs [18, 19]. On the other hand, unguided self-help programs have the advantage that they are less costly and better scalable [20]. One promising approach, possibly combining the benefits of both guided and unguided self-help programs, is the use of guidance on demand [21]. Guidance on demand implies that support from a therapist is only established when requested by a participant. An internet-based self-help program for increased self-criticism with guidance on demand showed promising results [22]. Nonetheless, an internet-based self-help program for symptoms of anxiety and/or depression based on problem-solving therapy with guidance on demand had the same effect as the unguided version of the same program [23]. Likewise, an internet-based self-help program for tinnitus-related distress based on CBT with guidance on demand did not differ in its effectiveness from the unguided version of that program [24].

To the best of our knowledge, there is no study that has evaluated an internet-based self-help intervention for psychological distress due to COVID-19 in the general population yet. However, an internet-based self-help intervention for patients diagnosed with COVID-19 experiencing psychological distress has been evaluated in a small randomized controlled trial (RCT) [25]. The internet-based self-help intervention consisted of audio-recorded instructions focusing on relaxation, self-care, and a rising sense of security, which were uploaded online. Over a 2-week period, participants in the intervention group listened to the instructions via their mobile phone and performed a daily task, which took about 50 min. The intervention addressed COVID-19 patients with mild-to-moderate depression and/or anxiety symptoms. The average age of the 26 participants was 44.7 years; 62% were male and 38% were female. Ninety-two percent of the participants experienced at least mild depression symptoms and 62% experienced at least mild anxiety symptoms. Participants in the intervention group showed a significant reduction in depression and anxiety symptoms compared to the control group [25] .

Against this background, we developed an internet-based self-help intervention with guidance on demand called ROCO. This intervention specifically addresses individuals experiencing psychological distress due to the COVID-19 pandemic. Hence, the study aims to evaluate the efficacy and feasibility of the internet-based self-help program ROCO for people with psychological distress due to the COVID-19 pandemic.

### Objectives {7}

The specific objectives of the study are:
To evaluate the effects of the internet-based self-help program compared with a waiting control condition on:
The primary outcome depressive symptomsSecondary outcomes such as anxiety and stress symptoms, well-being, embitterment, and lonelinessTo evaluate the acceptance and user-friendliness of the internet-based self-help program and drawing conclusions for further developments of the program.To exploratory search for predictors, moderators, and mediators for the efficacy of the program:
e.g., optimism, age, severity of depressive symptoms, and frequency of use of the program

### Trial design {8}

The study is a parallel group RCT comparing an internet-based self-help intervention combined with care as usual (CAU) to a waiting control condition with only CAU. The study flowchart is displayed in Fig. 1. Participants in the waiting control condition receive access to the intervention 3 weeks after the baseline questionnaire. Eligible participants are randomly allocated to one of the two conditions in a 1:1 allocation ratio.

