**Fig. 1 Fig1:**
[figure not shown]
Flowchart of the study design

The aim of the RCT is to show the superiority of the internet-based self-help intervention combined with CAU to only CAU at the 3-week post assessment. Additionally, there will be 2 follow-up measurements after 6, respectively 18 weeks after the baseline questionnaire. Since at the time of the follow-up measurements both groups have used the internet-based self-help intervention, the groups can no longer be compared. However, we use these follow-up measurements to assess the sustainability of potential treatment gains, i.e., to examine whether the short-term effects of the internet-based self-help intervention are maintained within groups. In addition, the follow-up measurements will be used to explore predictors of the sustainability of potential treatment effects.

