## Interventions

### Explanation for the choice of comparators {6b}

The efficacy of the intervention is to be established. This is why we have chosen a waiting control condition as comparator. However, both the participants in the waiting control condition as well as in the intervention condition receive CAU, whereby CAU can range from no treatment at all to psychotherapy and/or drug therapy. Participants in the waiting control condition receive access to the internet-based self-help program after a waiting period of 3 weeks. We decided to give participants in the waiting control condition access to the program after only 3 weeks since, due to the pressing situation surrounding the COVID-19 pandemic, we wanted to give all participants access to psychological support as fast as possible. However, this has the implication that only short-term effects of the intervention can be assessed.

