### Outcomes {12}

All assessments are carried out online via self-observation questionnaires. The baseline measurement is at *t*_*0*_, the post-measurement *t*_*1*_ is at 3 weeks, the first follow-up measurement *t*_*2*_ is at 6 weeks, and the second follow-up measurement *t*_3_ is at 18 weeks after the baseline. Validated German versions of the questionnaires are used. For an overview of all outcome measures and corresponding measurement time points, see Fig. 2.

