##### Adherence

The intensity and frequency of use of the self-help program is measured by indicators collected within the self-help program such as percentage of accessed pages or number of logins.

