### Plans to promote participant retention and complete follow-up {18b}

The participants are asked by e-mail to complete the online questionnaires. If participants fail to complete a questionnaire, they will be reminded by e-mail to do so: for post measurement, they will be reminded after 5 and 10 days and for follow-up measurements after 7 and 14 days. All participants are asked to complete the online questionnaire at each point of measurement, regardless of protocol adherence or any previously uncompleted online questionnaires.

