## Statistical methods

### Statistical methods for primary and secondary outcomes {20a}

We will use linear mixed models with time (pre versus post-intervention measures) as a within-group-factor and study condition (immediate access versus control condition) as a between-group-factor to evaluate the efficacy of the internet-based self-help intervention. This primary analysis will be performed using the data from the baseline and the 3-week post assessment. To analyze the stability of the short-term effects of the internet-based self-help intervention, we will conduct within-group analyses using repeated measures ANOVA (pre-intervention, post-intervention and follow-up measures) and paired *t* tests when comparing only two time points.

Moreover, we will exploratory analyze possible predictors, mediators, and moderators for the relationship between the internet-based self-help program and the outcomes. The significance level is set at 5%. Analyses will be conducted using SPSS and R.

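### Controls get program access at week 3, when the primary assessment falls due and is then chased for 10 more days, so late control answers may follow first use and dilute the only randomised comparison

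*Protocol article*

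**What the plan says.** Control access is tied to the calendar in two places. Trial design {8} states: "Participants in the waiting control condition receive access to the intervention 3 weeks after the baseline questionnaire". Explanation for the choice of comparators {6b} repeats it: "Participants in the waiting control condition receive access to the internet-based self-help program after a waiting period of 3 weeks".

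The primary assessment falls at the same point. In Outcomes {12}, t1 "is at 3 weeks, the first follow-up measurement" being placed at 6 weeks. Collection of t1 does not end there. Under Plans to promote participant retention {18b}, non-completers are chased: "for post measurement, they will be reminded after 5 and 10 days". The same section adds: "All participants are asked to complete the online questionnaire at each point of measurement, regardless of protocol adherence".

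The efficacy claim rests on t1. Trial design {8} aims to show superiority of the program plus care as usual (CAU) "to only CAU at the 3-week post assessment", and Statistical methods {20a} says: "This primary analysis will be performed using the data from the baseline and the 3-week post assessment". Section {20c} adds intention to treat and multiple imputation. Neither section separates control answers given before access from those given after it.

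**The concern.** Three stated rules overlap: access at week 3, t1 at week 3, and requests for t1 for at least 10 days after that. Followed literally, they allow a control to open the program first and fill in t1 afterwards. That score would count as CAU alone although the participant had begun the intervention.

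The article itself accepts the principle. Trial design {8} rules out between-group comparison at 6 and 18 weeks because both arms will have used the program by then. The same reasoning applies to any control whose t1 answer follows first use. Since t1 is the only randomised contrast, the overlap touches the primary endpoint and every secondary outcome compared between arms. The expected direction is dilution, which costs power.

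**Working it through.** **Timeline.** I assume the reminder days count from the week-3 invitation. Control access is then due on day 21 and t1 on day 21, with reminders on day 21 + 5 = 26 and day 21 + 10 = 31. An answer prompted by a reminder comes at least 5 or 10 days after access was due, which is 5/21 = 24% or 10/21 = 48% of a 3-week program. No closing date for t1 is given, so later answers are possible.

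**The plan's own figure.** Inputs from Sample size {14}: alpha 0.05, power 0.80, d = 0.35, r = 0.4, and a within-between interaction in a repeated-measures ANOVA. With two groups and two measurements:

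- f = d/2 = 0.175
- λ = f² × N × 2 / (1 − r) = 0.030625 × 80 × 2 / 0.6 = 8.17, with 1 and 78 degrees of freedom
- power is 0.806 at N = 80 and 0.796 at N = 78

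The stated 80 is reproduced, with almost no reserve. I keep the plan's convention below only so that any change comes from dilution; whether that convention is the best one is a separate question.

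**Dilution.** Let p be the share of control t1 answers that are late, and g the fraction of the full effect a late control has gained on answering. The document gives neither. I assume p from 10% to 50%, and linear gain from day 21, so that g = days late / 21.

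Effective d = 0.35 × (1 − p × g). For p = 30% and 10 days: 0.35 × (1 − 0.30 × 0.476) = 0.300.

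| Late share p | Days late | Effective d | Power at N = 80 | N for 80% power |
|---|---|---|---|---|
| any | g = 0 | 0.350 | 0.806 | 80 |
| 10% | 5 | 0.342 | 0.787 | 84 |
| 10% | 10 | 0.333 | 0.767 | 88 |
| 30% | 5 | 0.325 | 0.746 | 92 |
| 30% | 10 | 0.300 | 0.677 | 108 |
| 50% | 5 | 0.308 | 0.701 | 102 |
| 50% | 10 | 0.267 | 0.576 | 136 |

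Each row supposes that every late control started on day 21 and was late by the same number of days. The calculation gives no extra gain to late answers in the intervention arm; any such gain would offset part of the loss.

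**The case against.** The strongest reply is that the sequence may already be controlled. The study flowchart and the SPIRIT schedule are not shown, and a separate full protocol exists. Any of them could release access only after t1 is completed, and then the problem vanishes for everyone who completes t1. The stated aim of comparing with CAU alone at t1 fits that intention. This stands, so it would be wrong to assert that the trial has no gate or no rule for late scores. What remains is that the visible text states both the access trigger and the reminder schedule, and as written they collide.

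The second reply is that access is not use. The program is self-paced with no scheduled contact, and someone who ignores t1 e-mails for a week may well be ignoring the program too. This also stands. A reader might infer that late control answers are in fact taken on treatment, but the document supports only that they may be.

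Third, the losses are scenarios. A reader might take 14% (0.35 to 0.30) or 24% (0.35 to 0.267) as estimates of what the trial loses. They are not: the late share, linear gain and immediate start are all assumed, and zero loss is compatible with the text.

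Fourth, a reader might conclude that exposed control scores should be dropped from the primary analysis. That would discard observed outcomes in one arm only, on the basis of behaviour after randomisation. It would sit badly with the intention-to-treat plan, add to an anticipated attrition of 5.4–45.5%, and could exchange conservative dilution for selection of unknown direction.

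**Conclusion.** The point holds as a conflict of timing between stated rules. Control access and t1 share the same due date, t1 is still requested 5 and 10 days later, and no visible section makes access follow t1. Controls who answer late may have started the program, which would bias the only randomised contrast towards no difference.

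The size is unknown. On the assumptions above, d lies between about 0.34 and 0.27, and power at the planned N of 80 between about 0.79 and 0.58. The loss is nil if late controls have not used or benefited from the program. The document gives no ground for expecting a falsely positive result from this source. The matter is worth settling because the remedy is cheap and the article reports recruitment still open (N = 99 in January 2021, completion expected in April 2021).

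**What to change.** 1. **Controls still to reach week 3:** present the t1 questionnaire at or before first entry to the program, or state that this is already done. The date on which access falls due need not change.
2. **Participants already past t1:** keep the intention-to-treat analysis of all observed t1 scores as primary, and report the day of t1 completion by arm.
3. **Sensitivity analysis, specified before the data are analysed:** treat control t1 scores given after first login as missing under the multiple imputation already planned, and set the result beside the primary one. This needs dated t1 completions and first logins. The Adherence section mentions only "indicators collected within the self-help program such as percentage of accessed pages or number of logins", so first establish whether those dates were stored. If they were not, say so and report what is available.

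The cost is one questionnaire step before program entry for the remaining controls and a little extra analysis. No observed score leaves the primary analysis.

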**Fig. 1 Fig1:**
[figure not shown]
Flowchart of the study design

The aim of the RCT is to show the superiority of the internet-based self-help intervention combined with CAU to only CAU at the 3-week post assessment. Additionally, there will be 2 follow-up measurements after 6, respectively 18 weeks after the baseline questionnaire. Since at the time of the follow-up measurements both groups have used the internet-based self-help intervention, the groups can no longer be compared. However, we use these follow-up measurements to assess the sustainability of potential treatment gains, i.e., to examine whether the short-term effects of the internet-based self-help intervention are maintained within groups. In addition, the follow-up measurements will be used to explore predictors of the sustainability of potential treatment effects.

## Methods: participants, interventions, and outcomes

### Study setting {9}

The single study center is located at the University of Bern, Switzerland. All data is collected online using questionnaires programmed in Qualtrics [26]. Data is collected in German-speaking areas (i.e., Switzerland, Germany, Austria, and Liechtenstein).

### Eligibility criteria {10}

All interested persons must provide full written informed consent and are required to complete a baseline-screening questionnaire prior to randomization to assess eligibility.

Inclusion criteria are:
To be at least 18 years oldTo exceed a cutoff value of 4 points on the brief Patient Health Questionnaire (PHQ-9) [27]To be able to specify an emergency address in the event of an acute crisisTo have access to the internetTo understand and master the German language to the degree that one understands the content and instructions of the study

Exclusion criteria are:
The presence of suicidal tendencies (score ≥ 8 on the Suicide Behavior Questionnaire Revised (SBQ-R) [28]A known diagnosis of a psychotic or bipolar disorder

## Who will take informed consent? {26a}

Individuals interested in participating in the study can provide their e-mail address on the study homepage. Subsequently, they receive an e-mail with the detailed study information and the informed consent form. They are also asked to watch a video on the study homepage in which the study information is explained orally by the principal investigator. Individuals have the possibility to ask the study team questions about the study via e-mail. Written informed consent is obtained from individuals willing to participate in the study by the Principal Investigator.

### Additional consent provisions for collection and use of participant data and biological specimens {26b}

Not applicable as no ancillary studies are performed.

## Interventions

### Explanation for the choice of comparators {6b}

The efficacy of the intervention is to be established. This is why we have chosen a waiting control condition as comparator. However, both the participants in the waiting control condition as well as in the intervention condition receive CAU, whereby CAU can range from no treatment at all to psychotherapy and/or drug therapy. Participants in the waiting control condition receive access to the internet-based self-help program after a waiting period of 3 weeks. We decided to give participants in the waiting control condition access to the program after only 3 weeks since, due to the pressing situation surrounding the COVID-19 pandemic, we wanted to give all participants access to psychological support as fast as possible. However, this has the implication that only short-term effects of the intervention can be assessed.

